### Ethical considerations and dissemination

2.3.

Approval will be obtained from the ethics committees of all institutions where the study will be carried out. All participants will be informed of the study’s objectives, methodology, benefits, and possible risks. All participants will sign a written informed consent expressing their agreement to participate in this study. Participants’ confidentiality will be ensured during all study procedures. Participants will be informed that they may withdraw their participation at any time without penalty or other consequence. Only research team members and healthcare professionals who care for participants have access to participant data. This data will be destroyed 5 years at the end of the study. If there is a need to change planned procedures, and that may have an impact on the execution of the study (e.g., changes in the study design, in the study objectives and in the study procedures), they will be reviewed by independent investigators and communicated to the ethics committees of all institutions where the study was carried out. The results of the study will be disseminated through oral communications and posters at conferences, and publications in scientific journals.

### Validity and reliability/rigour

2.4.

Variables such as educational level, duration of mental disorder, and type of treatment may influence the results of this study. The proposal to use the stratified random sampling method in this study aims to minimize confounding bias. All procedures, including the implementation of the intervention will be carried out after trainers have completed MCT-Silver training to minimize the risk of bias. Participants will be randomly allocated to either the experimental group [MCT-Silver + Treatment As Usual (TAU)] or the control group (TAU only). A computer-generated stratified random sampling method will be applied taking into consideration an equitable distribution by sex and age to promote sex and age equality and inclusiveness. Finally, all raters will be blinded to participant group assignment.

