#### Randomization and blinding

2.2.3.

Eligible participants will be recruited at each institution (the mental health service of each hospital that agreed to take part in the study in Portugal) through telephone contact by the researchers in collaboration with the multidisciplinary team. The study will also be publicized in the media so that older adults can contact the researchers if they are interested in participating. A baseline assessment will be carried out and all instruments will be applied after informed consent from participants. All participants who agree to participate in the study will be assigned a code and will be randomly assigned to either MCT-Silver (experimental group where the intervention will be applied) or the control group (no stratification factors). This randomization will be performed using a computer program. The control group will not be administered the intervention (MCT-Silver). In both groups, treatment will be maintained as usual (Treatment As Usual – TAU) and participation in other interventions as well as use of medications will be carefully monitored. Study participants will be informed that they should not reveal which group they are in and will be reminded of this at each testing session. All participants will be re-assessed at the end of the intervention and 3 months after completion, with the application of all planned instruments. Assessments will be performed by the same rater before and after the intervention and at follow-up. Assessors will be trained in the administration of all instruments prior to the start of the study. A third researcher will inform patients of group assignment so that raters will remain blinded throughout the study. The Side Effects of Intervention questionnaire and patient satisfaction with MCT-Silver will be applied to the experimental group post-intervention (Table 1; Figure 1).

**Table 1 tab1:** Study schedule.

	Study period				
	Enrolment	Randomization	Intervention (8 weekly sessions)	Post (8 weeks)	Follow-up (3 months)
TIMEPOINT	T-1	T0		T1	T2
Enrolment:					
*Eligibility screen*	X				
*Informed consent*		X			
*Randomization*		X			
Interventions:					
*Treatment As Usual (TAU)*	X	X	X	X	X
*MCT-Silver*			X		
Assessments: *Baseline*		X			
*Post-intevention*				X	
*Follow up*					X

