##### Treatment as usual

2.2.5.1.

All participants (experimental and control group) will continue to receive treatment as usual (TAU) at their institution. TAU may consist of psychiatric and psychosocial treatment by a multidisciplinary team, which includes mental health psychiatric nurses, psychiatrists, psychologists, social workers, occupational therapists and other mental health professionals. TAU may also include treatment in community settings, day hospital and inpatient settings, as well as antidepressant medication, psychosocial rehabilitation, socialisation groups and psychoeducational and therapeutic groups. The care of participants in TAU will not be limited or influenced in any way. To control for TAU, we will carefully record participation in concurrent treatment. The control group will not participate in the MCT-Silver programme.

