#### Data collection and outcome measures

2.2.6.

The instruments will be administered to all study participants through an interview at three planned assessments (Table 3). To characterize the sample, sociodemographic, and clinical data will be collected [age, sex, marital status, cohabitation, educational level, professional/employment status, duration of depression diagnosis (if applicable), number of psychiatric hospitalizations, medication, type of treatment, and substance use; Table 4]. These data will be collected before the start of the MCT-Silver intervention for all participants.

**Table 3 tab3:** List of study measures and questionnaires.

Instruments	Baseline	8 weeks (post)	3 months (follow-up)
Mini Mental State Examination	X		
Beck’s Depression Inventory (BDI-II)	X	X	X
Patient Health Questionnaire (PHQ-9)	X	X	X
Montgomery-Asberg Depression Rating Scale (MADRS)	X	X	X
Metacognitions Questionnaire (MCQ-30)	X	X	X
Dysfunctional Attitudes Scale (DAS-18B)	X	X	X
WHOQOL-BREF Item 1	X	X	X
Ruminative Response Scale (ERR-10-A)	X	X	X
Rosenberg Self-Esteem Scale	X	X	X
The Attitudes to Ageing Questionnaire (AAQ-12)	X	X	X
Intervention questionnaire and patient satisfaction		X	X

**Table 4 tab4:** Summary of the clinical and demographic characteristics of the sample.

Questions	Answers						
Age							
Gender	Female	Male					
Marital status	Single	Married/ marital partnership	Widowed	Divorced/separated			
Level of education	Cannot read or write	Can read and write, but has not attended school	Attended school, but not higher education	Number of years of schooling	Higher education		
Who you live with	Institution	Alone	Spouse/partner	Child	Brother/sister	Other relative	Other non-family member
Labour status	Employed	Unemployed	Retired	Retired on invalidity	On sick leave	Current or past occupation	
Do you take any medication? If yes, which one?	No	Yes	If so, which one?				
Have you ever been admitted to a psychiatric ward?	No	Yes	How many times?				
Have you ever been to a psychiatric day hospital?	No	Yes	How many times?				
Are you followed up in follow-up appointments/ programmes?	No	Yes	Which ones?				
What is your current substance consumption?	None	Tobacco	Alcohol (more than 3 drinks a day)	Other drugs, which ones?			
Do you have any diagnosed illness(es)?	No	Yes	If so, which one or ones?				

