#### Data analysis

2.2.9.

The data will be analysed using Statistical Package for Social Sciences software (SPSS®) version 24.0 for Windows. Descriptive analysis will be used to characterize the sample. Within-group differences (t0 to t1 and t0 to t2) will be examined using paired sample *t*-tests. To evaluate change in primary and secondary outcomes between the two groups, we will perform ANCOVAs with treatment as the between-subject factor (MCT-Silver + TAU vs. TAU), the difference score of the outcomes (t1 – t0 and t2 – t0, respectively) as the dependent variable, and the baseline score of the respective outcome as the covariate. We chose ANCOVAs with difference scores instead of a repeated measures ANOVA to avoid regression to the mean and to control for potential baseline differences.

Intention-to-treat (ITT) analyses (including all participants who provided baseline data) using multiple imputation (MI) will be conducted. Analyses utilizing a complete cases sample (CC; including only complete data—i.e., baseline, post, and follow-up) will also be conducted. We will use analogous models to assess changes (t0-t1; t0-t2) for the secondary outcomes (WHOQOL-BREF item 1, DAS-18B, ERR-10-A, AAQ12, MCQ-30, MADRS, PHQ-9, RSE). We will also conduct planned moderation analyses for the primary outcome at post-assessment (BDI-II). Demographic characteristics (age, sex, education) and clinical characteristics (previous or current treatment, comorbid anxiety disorder, number of sessions attended) as well as baseline scores on secondary outcomes (WHOQOL-BREF item 1, DAS-18B, ERR-10-A, AAQ12, MCQ-30, MADRS, BDI, RSE) will be examined separately using moderation models as defined as defined by the PROCESS SPSS macro (model 1) [59]. Self-rated depression difference scores (t0–t1 and t0–t2) will be entered as the dependent variable (Y) and depression severity at t0 as the covariate.

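### Section 2.4 names education, duration of illness and type of treatment as influential, but neither the stratification it cites nor the efficacy ANCOVA acts on any of them

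*Protocol article*

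**What the plan says.** Section 2.4 (Validity and reliability/rigour) opens with the three variables: "Variables such as educational level, duration of mental disorder, and type of treatment may influence the results of this study". The next sentence reads "The proposal to use the stratified random sampling method in this study aims to minimize confounding bias". Later in the same paragraph the stratification is specified as "taking into consideration an equitable distribution by sex and age to promote sex and age equality and inclusiveness". No other factor is given.

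Section 2.2.3 (Randomization and blinding) describes computer randomisation with "no stratification factors".

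Section 2.2.9 (Data analysis) defines the efficacy model as an ANCOVA of the change score on treatment, "and the baseline score of the respective outcome as the covariate". Education and previous or current treatment appear in that section only as moderators of the BDI-II change, each in its own model. Duration of illness appears in no analysis.

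Section 2.2.6 (Data collection and outcome measures) lists baseline data that include "duration of depression diagnosis (if applicable), number of psychiatric hospitalizations, medication, type of treatment" and refers to Table 4. Table 4 has no row for duration and none for current treatment setting. It asks about medication, whether the person was ever admitted or ever attended a day hospital, and follow-up programmes.

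Section 2.2.5.1 shows how much usual care may vary: "TAU may also include treatment in community settings, day hospital and inpatient settings, as well as antidepressant medication".

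**The concern.** The plan names three variables, follows them with a safeguard, and then defines that safeguard on two other variables. Another section denies that the safeguard exists, and the efficacy model contains none of the three. A reader of section 2.4 would think education, duration and type of treatment had been dealt with in the design.

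Two things are at stake. First, prognostic variance that could be removed stays in the error term, so the trial is somewhat less precise than its own data allow. Second, if the arms differ by chance on one of these variables, the efficacy estimate carries that difference. With no adjustment set fixed in advance, a later correction would look like a choice made after seeing the data. Now is a good time to settle it, because the pilot is still in preparation and the RCT sample size has not been set (sections 1 and 2.2.4).

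**Working it through.** The article gives no RCT sample size, SD, alpha or power (section 2.2.4 defers them to the pilot), so there is no figure of the plan's own to reproduce. The check has a reading part and an illustrative part.

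**1. The sections side by side, for the three named variables**

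- Education: not a stratification factor; not in the ANCOVA; a separate moderator in 2.2.9; on Table 4.
- Type of treatment: not a stratification factor; not in the ANCOVA; previous or current treatment is a separate moderator; listed in 2.2.6, but Table 4 has no current-setting row.
- Duration of illness: not a stratification factor; not in the ANCOVA; not a moderator; listed in 2.2.6, but Table 4 has no row.
- Sex and age: stratified according to 2.4, not stratified according to 2.2.3; separate moderators only.

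A moderation model asks whether the effect differs by the variable. It does not adjust the main efficacy estimate.

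**2. Does the omission bias the comparison?**

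Inputs (all assumed): equal arms; total N of 32, 60 or 100; a baseline score; three independent prognostic variables that together explain R² = 0.10 or 0.30 of the variance left after baseline; two-sided alpha 0.05; 6,000 simulated trials per setting with no treatment effect.

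- Baseline-only ANCOVA: mean estimate within 0.006 SD of zero; type I error 4.8–5.6%.
- With the three variables added: type I error 4.5–5.5%.

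There is no systematic confounding.

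**3. How large can chance imbalance be?**

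For one standardised variable with n per arm, the SD of the between-arm difference is √(2/n). The probability p of a difference above 0.5 SD is 2[1 − Φ(0.5/√(2/n))]. For at least one of three independent variables it is 1 − (1 − p)³.

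| Total N | √(2/n) | p, one variable | any of three |
|---|---|---|---|
| 32 | 0.354 | 15.7% | 40% |
| 60 | 0.258 | 5.3% | 15% |
| 100 | 0.200 | 1.2% | 3.7% |
| 200 | 0.141 | below 0.1% | 0.1% |

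Illustration: if acutely ill or inpatient participants improved by 0.5 SD more (assumption) and their share differed by 15 percentage points between arms, the estimate in that trial would shift by 0.5 × 0.15 = 0.075 SD. If 30% of participants are of this kind (assumption), the SE of the difference in shares is √(2 × 0.3 × 0.7/n). A gap of 15 points or more then has a probability of about 35% at N = 32, 20% at N = 60 and 10% at N = 100.

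**4. What would adjustment gain?**

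In large samples the confidence interval narrows by 1 − √(1 − R²):

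- R² = 0.05: 1 − √0.95 = 2.5%
- R² = 0.15: 1 − √0.85 = 7.8%

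Starting from 80% power at two-sided 0.05, power with adjustment is Φ((1.960 + 0.842)/√(1 − R²) − 1.960). That is about 82% at R² = 0.05 and 84% at R² = 0.10.

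Small samples give less, because the covariates use degrees of freedom. Simulated SE of the treatment effect, baseline-only then adjusted:

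| Total N | R² = 0.10 | R² = 0.30 |
|---|---|---|
| 32 | 0.359 → 0.362 | 0.361 → 0.317 |
| 60 | 0.261 → 0.255 | 0.257 → 0.220 |
| 100 | 0.204 → 0.195 | 0.203 → 0.171 |

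At R² = 0.10 there is no gain at N = 32, about 2% at N = 60 (0.006/0.261) and about 4% at N = 100 (0.009/0.204). The R² = 0.30 column lies outside the 5–15% range and shows only that the gain grows with R².

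**The case against.** The strongest reply is that an ANCOVA on the baseline outcome score is a valid analysis of a randomised trial. The choice of further covariates is a preference, and its benefit rests on an R² the documents do not give. Chance imbalance is already part of what the standard error measures, so the 0.075 SD figure describes one unlucky draw and not a bias. All of this stands, and it limits the point to precision and prespecification.

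It can also be said that section 2.4 does not state which confounding the stratification is meant to reduce; the link to the three variables comes from the adjoining sentence. Nor need stratified sampling mean stratified allocation: it could describe how people are selected, which would soften the conflict with 2.2.3. Both readings are possible. But stratified selection would not balance the arms on anything, so under either reading the three variables get no protection and the wording needs repair.

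Two stronger conclusions are tempting. A reader might infer that differing natural courses are left uncontrolled and that the effect estimate is confounded. The documents do not support that: allocation is random, the control arm is concurrent and both arms receive usual care. Section 2.2.5.1 says only what usual care may include; it gives no case mix and no difference in course.

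A reader might also infer that duration will go unrecorded and that the gap could never be filled. That overreads Table 4, which is captioned as a summary of sample characteristics and is not called the case report form. The text of 2.2.6 commits to collecting duration, and 2.2.3 and 2.2.5.1 commit to recording concurrent treatment. What is shown is a mismatch between text and table.

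**Conclusion.** The point holds as an inconsistency with a modest statistical cost. The plan calls three baseline variables influential, cites a safeguard that does not act on them and that 2.2.3 appears to deny, and then fits an efficacy model without them. The comparison remains valid.

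The loss is an interval about 2.5–8% wider than it need be in a reasonably large RCT, if the three variables explain 5–15% of residual variance, plus chance imbalance with no adjustment fixed in advance. At the pilot's 32 participants, adjustment brings little or nothing within that range. The figures rest on assumed R², equal allocation and independent covariates; none of these comes from the documents. The change is worth making because it is cheap and can still be settled before the RCT is sized.

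**What to change.** 1. **Section 2.2.9.** For the RCT, prespecify a small covariate set in the primary and analogous ANCOVAs and in the imputation model: years of education, duration of depression and baseline treatment type, besides the baseline score. Use pre-randomisation values only, because concurrent treatment recorded later may itself be affected by allocation. Because 2.2.6 collects duration only where applicable, say how people without a previous diagnosis are coded. If the authors prefer the baseline score alone, they should say that randomisation alone handles these variables.
2. **Table 4.** Add duration of depression and current treatment type or setting, so that the table matches 2.2.6.
3. **Sections 2.2.3 and 2.4.** State once whether allocation is stratified and by what. Remove any suggestion that stratification deals with the three named variables. If sex and age are stratified, include them in the ANCOVA.

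Cost: wording, two items on the baseline form and a few degrees of freedom (three or four for the named variables with treatment type at two or three levels; two more if sex and age enter as one term each). No extra participants or visits are needed.

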## Discussion

3.

MCT-Silver is a low intensity, CBT-based group intervention, which appears to have great potential in reducing depressive symptoms but further studies are needed to better validate its efficacy as the pilot study was limited due to lack of a control group (Schneider et al., 2018) as well as the lack of follow-up assessments. Only one RCT on MCT-Silver has been conducted (in Germany) (Schneider et al., under review).^3^ The efficacy of MCT-Silver for older adults with depression has not yet been studied in the Portuguese population and, therefore, the development of the present trial is essential.

Portugal is one of the countries of the Organization for Economic Co-operation and Development (OECD) with the highest consumption of antidepressants (OECD, 2019) and, despite international guidelines recommending complementary treatment with non-pharmacological interventions (American Psychological Association, 2019), in Portugal this practice is not common. Most people with depression are only treated with medications.

It is expected that the results of this trial will provide support for the efficacy of the Portuguese version of MCT-Silver on the reduction of depressive symptoms. Moreover, it is anticipated that participants in the MCT-Silver group will demonstrate greater reductions in metacognitive beliefs, dysfunctional attitudes, ruminative responses and (negative) attitudes towards aging, as well as greater improvements in quality of life and self-esteem compared to a TAU group. The results of this trial are expected to allow future implementation of MCT-Silver by mental health and psychiatry professionals in various contexts. The MCT-Silver programme aims to contribute to the psychosocial rehabilitation of older adults with depression. The trial illustrated in this protocol intends to assess the efficacy of MCT-Silver in the Portuguese population.

Since people with depression often have cognitive deficits (Muhammad and Meher, 2021), patients with significantly impaired cognitive abilities may have difficulty understanding MCT-Silver exercises. To overcome this limitation, we will apply the MMSE to screen for cognitive deficits. Other limitations may be transportation difficulties getting to sessions regularly, as well as health problems, which may limit participation in the study or the changes in medication during the course of the study.

Minimal negative side effects of D-MCT have been previously reported (Dietrichkeit et al., 2021). We anticipate similar findings, such as disappointment that the training did not result in (greater) symptom improvement and being more burdened by symptoms because patients may think about them more during the training. Attendance (i.e., coming to appointments) may also be perceived as stressful. It is also possible that patients could experience a clinically significance worsening of symptoms. In this case, participation in the study would be discontinued and, if necessary, participants would be offered assistance in identifying needed treatment.

This study includes many measurement instruments and were chosen to improve comparability with previous trails on MCT-Silver and D-MCT (see Jelinek et al., 2015) (Schneider et al., under review, see footnote 3). Nonetheless, completion of study measures can be burdensome and time-intensive for participants. Given that this is the first MCT-Silver trial in Portugal and participants are receiving a psychological intervention, we believe that the potential knowledge to be obtained from the study justifies participants’ time and potential burden related to participation in the study. Additionally, participants are allowed to discontinue testing and will not be penalized for this. Use of self-report measures is common in RCTs of psychological interventions and provide indications regarding patients’ perceptions of symptoms and suffering from these symptoms. Nonetheless, responses are impacted by many factors, including social desirability and insight, as well as reading competence and motivation, which may limit the validity of our findings. For this reason, we have also included a clinician-rated measure of depression (MADRS). The results of the RCT will be implemented to improve the training, provide information regarding efficacy among Portuguese patients (vs. TAU) and, in the case of efficacy, to support dissemination and uptake in Portugal, which would lead to a reduced treatment gap among older adults with depression.

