Metacognitive training for older adults with depression (MCT-Silver; Schneider et al., 2018; Bücker, 2019), is a cognitive-behavioral (CBT)-based group intervention, specifically designed for adults ages 60 years and older (all materials are available for free^1^). MCT-Silver aims to reduce the treatment gap by improving access to mental health care for the estimated 73% of older adults with depression who go untreated (Horackova et al., 2019). MCT-Silver is based on metacognitive training for psychosis (MCT; Moritz and Woodward, 2007) and metacognitive training for depression (D-MCT; Jelinek et al., 2015). Randomized controlled trials on D-MCT provide evidence for its efficacy on depressive symptoms (Jelinek et al., 2016), as well as metacognitive and negative cognitive beliefs (Hauschildt et al., 2022; Özgüç and Tanriverdi, 2022) at short- and intermediate follow-up intervals. Long-term efficacy of D-MCT remains equivocal (Jelinek et al., 2019). A pilot study examined the feasibility, acceptance, and effects of D-MCT as an add-on intervention in a group of older adults with depression who were completing an intensive inpatient treatment program (55+ years; *N* = 116). Per protocol analyses (*n* = 55) yielded a significant decrease in depressive symptoms (*d* = 1.06) and cognitive biases (*d* = 0.33). These results support the feasibility and acceptance of D-MCT among older adults with depression. A recently completed RCT in Germany, which compared MCT-Silver to an active control group (cognitive remediation; (Schneider et al., 2018)) yielded large and significant reductions on the primary outcome (Hamilton Depression Rating Scale) from baseline to post and 3-month follow-up (*d_MCT-Silver_* = 1.25 – 1.42; *d*_CR_ = 1.05 – 1.12). Group differences; however, did not reach significance (η_p_^2^ = 0.001 – 0.002). MCT-Silver yielded significant moderate to large effects compared to CR immediately following the intervention and after 3 months for self-reported depression (BDI-II: η_p_^2^ = 0.075 – 0.135) and rumination (RRS: η_p_^2^ = 0.087 – 0.127). A significant moderate effect was found for positive metacognitive beliefs (MCQ-PB) at post-assessment (η_p_^2^ = 0.067), but group differences did not reach significance at follow-up (η_p_^2^ = 0.027). Small reductions in negative cognitive beliefs (Dysfunctional Attitudes Scale-18B) at post- and at 3-month follow-up (*d_MCT-Silver_* = 0.24 – 0.30) were found for the MCT-Silver group, whereas negative cognitive beliefs were unchanged in the CR group (*d_CR_* = –0.06 – 0.06).

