**Figure 2 fig2:**
[figure not shown]
Example of Module 7: Jumping to Conclusions.

Through interactive exercises and a structured multimedia presentation, MCT-Silver aims to convey knowledge about cognitive distortions, helps participants to reflect critically about and change the content of their thoughts, and acquire new strategies to solve problems. Each session lasts 45–60 min (Jelinek et al., 2022).

In the current study, MCT-Silver will be applied to the experimental group by mental health and psychiatry professionals with experience in the care of individuals with depression. A training course on the application of the MCT-Silver programme will be completed by these professionals prior to the start of the study. Administration of the training will also be monitored and supervised by the study PI ([name]). For adherence monitoring of the MCT-Silver application the sessions will be recorded, and no images of the participants will be taken to safeguard ethical issues.

MCT-Silver sessions will be applied once a week for a total of eight sessions. The intervention will be applied face-to-face in groups in a quiet room of the institution to which the group belongs.

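### The Discussion ends study participation, not only the training, when depression clearly worsens; if followed, T1 and T2 outcomes are lost in patients selected on the construct the primary outcome measures

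*Protocol article*

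**What the plan says.** The Discussion (section 3), in its paragraph on side effects, allows that patients may get worse: "It is also possible that patients could experience a clinically significance worsening of symptoms". It then gives the consequence: "In this case, participation in the study would be discontinued and, if necessary, participants would be offered assistance in identifying needed treatment". No instrument, threshold, timing or arm is attached to this rule.

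Section 2.2.3 sets the general schedule: "All participants will be re-assessed at the end of the intervention and 3 months after completion, with the application of all planned instruments". It does not mention participants who have been discontinued.

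Section 2.2.6 places the measurements: "The instruments will be administered to all study participants through an interview at three planned assessments (Table 3"). Table 3 puts them at baseline, 8 weeks (T1) and 3 months after the intervention (T2), with nothing between baseline and T1. Under section 2.2.5.2, "MCT-Silver sessions will be applied once a week for a total of eight sessions", and only the experimental arm attends them.

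Section 2.2.9 plans two analysis sets. The first: "Intention-to-treat (ITT) analyses (including all participants who provided baseline data) using multiple imputation (MI) will be conducted". The second: "Analyses utilizing a complete cases sample (CC; including only complete data—i.e., baseline, post, and follow-up) will also be conducted". The model is an ANCOVA of the difference score on arm, with the baseline score as covariate.

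**The concern.** Stopping a treatment and leaving a trial are different events. A patient who stops the sessions can still be measured. A patient whose participation in the study has ended, on the ordinary meaning of the words, is not. For patients who worsen, the Discussion and section 2.2.3 therefore give site staff two different instructions.

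The trigger is depressive worsening and the primary outcome is change in BDI-II, so the rule would select for loss on the construct that the trial measures. The case differs from voluntary withdrawal (section 2.3) because the symptoms, not the participant, decide. An analysis plan can choose how to model missing scores, but it cannot bring back scores that were never taken.

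**Working it through.** **What the two routes do to the data**

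1. *Worsening noticed before the next scheduled assessment.* The coming score is not recorded, and its absence is related to what it would have been. Before T1 only the baseline score is available for imputation. Between T1 and T2 the baseline and T1 scores are.
2. *Worsening first recorded at the T1 visit.* The T1 score exists and only T2 is lost. That loss depends on an observed value, so imputation with T1 in the model can handle it. The complete-case set requires all three time points, so it drops the patient's T1 score as well.

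**Size**

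The document gives no standard deviation, threshold, detection rate or RCT sample size, so there is no figure of the plan's own to reproduce. Every input below is an assumption for illustration.

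- Baseline SD 10, post SD 10.12, correlation 0.6. Change SD = √(100 + 102.4 − 2 × 0.6 × 10 × 10.12) = √81 = 9. Residual SD given baseline = 10.12 × √(1 − 0.36) = 8.1.
- Worsening means a rise of at least +5, +7 or +10 points. With a mean change of −6, the share above the threshold is P(Z ≥ 11/9), P(Z ≥ 13/9) or P(Z ≥ 16/9), which is about 11%, 7.4% or 3.8%.
- The planned ANCOVA was simulated with 2,000,000 per arm and imputation within arm.

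*Noticed before T1, removal in MCT-Silver only, no true effect.* Spurious benefit in BDI-II points, imputing from baseline:

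| Threshold | All noticed | Half | 25% | 10% |
|---|---|---|---|---|
| +5 | 1.64 | 0.75 | 0.36 | 0.13 |
| +7 | 1.16 | 0.53 | 0.27 | 0.11 |
| +10 | 0.63 | 0.31 | 0.15 | 0.06 |

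This table removes patients on the T1 change itself. Worsening seen in mid-course predicts T1 imperfectly. With a mid-course trigger correlated 0.7 or 0.5 with the T1 change, 1.64 falls to 1.12 or 0.80 (+5, all noticed), and 0.31 falls to 0.21 or 0.15 (+10, half noticed). With 10% to 25% noticed, the bias is about 0.03 to 0.25.

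*Noticed before T1, removal in both arms (trigger again the T1 change itself).* There is no bias if the true effect is 0. A true −5 is estimated as −3.69 (+5, all noticed) to −4.68 (+10, half noticed). With 10% to 25% noticed it is −4.74 to −4.92.

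*Noticed between T1 and T2, MCT-Silver only, no true effect.* Imputation uses baseline and T1, with a T1–T2 correlation of 0.7 and removal on the T2 change itself. At +5, all noticed, the spurious benefit at T2 is 1.27, against 1.64 with baseline alone in the first table, so the extra score corrects part of it. With 10% to 25% noticed it is 0.04 to 0.26.

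*First recorded at T1.* The multiple-imputation bias at T2 is 0.00 at all three thresholds. In the complete-case set, with every such case removed in both arms, a true −5 becomes −3.74 to −4.36 at T1 and −4.34 to −4.67 at T2, with no bias under the null. If only MCT-Silver cases were removed, the spurious benefit under the null would be 0.62 to 1.58 at T1 and 0.33 to 0.85 at T2.

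**Scale**

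The Introduction reports partial η² of 0.075 to 0.135 for the BDI-II against an active comparator. With d = 2√(η²/(1 − η²)), these give 0.57 and 0.79. Multiplied by the assumed residual SD of 8.1, they are about 4.6 and 6.4 points.

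**The case against.** The sentence is a remark about tolerability in the Discussion and may mean only that the training stops. The paragraph around it is about side effects of the training. The same section lists health problems that may limit taking part in the study alongside difficulty reaching sessions, and it speaks separately of participants choosing to stop testing. The Methods already re-assess everyone, and the ITT set includes everyone with baseline data. This reading is plausible but not established. Section 2.3 uses participation in the broad sense, and section 2.2.3 does not say what happens to a discontinued patient. Nor is this just detail left to a fuller protocol, since the article positively states that study participation ends.

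Three points on size do stand.

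- The trigger is undefined and need not be the BDI-II. A reader might infer that scores go missing because of their own values. The document supports only that missingness would be related to the unseen score.
- No instrument is scheduled between baseline and T1, so detection there would be ad hoc. That makes the columns for half or all cases noticed hard to reach.
- Removal in one arm is not stated. Weekly sessions give MCT-Silver patients more study contact, but section 2.2.5.1 gives TAU patients access to a multidisciplinary team, and section 2.2.3 monitors concurrent treatment and medication in both arms.

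**Conclusion.** The point holds as a conflict in the text that should be resolved before recruitment, with medium confidence because the looser reading remains possible. If the sentence is followed as written, the trial loses outcomes in patients whose depression is worsening. Multiple imputation then repairs the loss fully only where the worsening was recorded at T1 and T1 is in the imputation model.

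The likely size is modest. With 10% to 25% of cases noticed before the next assessment, the bias is at most a few tenths of a point, against an effect scale of about 4.6 to 6.4 points. In the imputed analysis, a spurious benefit of 1 point or more is a ceiling that needs near-complete detection in MCT-Silver only. A dilution of that size likewise needs near-complete detection in both arms.

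A reader might go further and conclude that the primary comparison is shown to favour MCT-Silver. The document does not support that. Trigger, detection rate and arm are unstated, and removal in both arms gives no bias under the null and shrinks a true effect. All magnitudes rest on the assumed SDs, correlations and thresholds.

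**What to change.** Replace the consequence in the Discussion with a statement that clinically significant worsening stops the MCT-Silver sessions, with help in finding care as now, and that the scheduled T1 and T2 assessments are still collected in both arms unless the participant declines or withdraws consent. Put the same sentence in section 2.2.3 so that the two places agree.

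The cost is that wording and matching consent text, with no new visits. The small downside is assessment burden on participants who have worsened, who remain free to decline. If the sponsor already meant this, the change only makes it explicit.
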